### Participants

Participants are adults who reside in a study park’s zone of influence, which is deemed to be 0.5 km (0.31mi), which is an approximate 15-min walk to the park and also a reasonable maximum distance for hearing birdsong in an urban setting [45]. Participants will be recruited from within a 16-cell grid (120m^2^/cell) around each park. Thus, the unit of measurement is the individual, but the unit of assignment-to-intervention is neighborhood. We conducted a pilot study in two neighborhoods in 2018 (*n* = 67 participants enrolled) and received funding at the end of the summer in 2019, yielding a truncated field season (*n* = 145 participants). The first full field season for this study will be 2020. To recruit participants, we mail postcards and conduct recruitment activities (e.g., information booths) in each neighborhood. Field staff then visit homes in each study neighborhood to brief potential participants on the study, request participation, and screen for inclusion. We recruit only one English-speaking male or female (≥ 18y) without mobility issues per household, which is at the household’s discretion. To ensure participant comprehension and confirm contact information, we use an electronic text message to finalize enrollment. Participants are then instructed on the correct usage of the accelerometer (Actigraph GT3X), Global Positioning System (GPS) device (Canmore) and cortisol sample collection and instructed that a study shuttle will take them to their scheduled health appointment in our study office. The target total sample is 450 adults to be recruited and retained. To retain participants, we will employ a set of strategies including: 1) sending holiday cards with neighborhood-level results; 2) sending birthday cards; and 3) sending periodic, brief surveys through StANDApp.

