#### Control description

In June 2018, we conducted extensive inventories of all nine parks at baseline, evaluating the following: bird species, plant species, and maintenance and usage of parks. Each park had 8–20 bird species, with American Robin and European Starling the most common. Plant diversity was low, with many invasive species and turf grass. Broken cement and signs of dumping were common. Only one park was observed to be used by park-goers (see Fig. 2 for examples of current park conditions). We expect the CNT parks in this project to continue these conditions and to remain unmaintained (only mowed once annually) during the duration of the study.

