#### Measurement protocol

All items to be assessed are in Table 1 and include both individual and area-level measures. At recruitment, accelerometers (Actigraph GT3X) and GPS devices (Canmore) on an elastic belt and saliva collection kits will be distributed, and data will be collected for the following week. For subsequent time points, participants will be phoned to arrange an equipment delivery time and schedule a health appointment. Participants will be reminded via StANDApp (detailed below) and/or text to wear the elastic belt and to collect saliva samples. Participants will also take a paper survey at home. Participants will return the equipment, survey and saliva kits at the health appointment or, if they forget an item, will schedule a time to return the item(s) in order to receive the compensation voucher.

**Table 1 Tab1:** Tools, scale of measurement, and measurements that will be obtained annually 2019–2024. Individual-level refers to measurements collected from individual household participants and area-level refers to measurements collected within and at some points around a park

Tool/Variable	Individual or area-level	Measures obtained
Survey	Individual	Demographics, perceptions of neighborhoods, disease and medication history, diet, perceived stress score, anxiety and depression symptoms, nature-relatedness, perceived safety, acute illness
Physical activity (PA)	Individual	Total activity counts, Moderate-to-vigorous PA, when combined with GPS – green PA
GPS	Individual	Time spent in park, time spent in view of park, when combined with PA – green PA
Cortisol samples	Individual	Total concentration, slope of cortisol from waking to evening
Dried blood spots	Individual	C-reactive protein
Finger-stick A1C	Individual	Hemoglobin A1C levels
Plant surveys	Area	Plant diversity of park, invasive species versus native species
SOPARC	Area	Usage of park
Signs of care	Area	Maintenance level of park
Bird surveys	Area	Bird diversity of park
360 imagery	Area	Greenness of park, negative visual exposures, signs of disorder
AudioMoth acoustic recorders	Area	Bird species, insects, sound diversity, noise
Weather station	Area	Daily precipitation, high temperature

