We adopt a regression-based approach to multivariable modeling that addresses features of clustering of participants within parks and correlation over time in repeated assessments. Repeated measures ANOVA, or more apropos, generalized linear (mixed) models (GLMM) will be used [135–137]. Denote by $$ {\mathit{\mathsf{Y}}}_{\mathit{\mathsf{it}}} $$ an outcome in the *i*-th participant in the *h-*th park assessed at time *t*. It is assumed that an individual is primarily exposed to one park. Generally, outcomes are assessed at baseline and at least 3 additional time-points, denoted t = 0, 1, 2, 3. Our hypotheses concern the expected response: $$ {\textsf{g}}\left({\mu}_{{\textsf{hi}\textsf{t}}}\right)={\mathbf{\textsf{x}}}_{{\textsf{it}}}^{\prime}\beta +\mathbf{\textsf{z}}{\hbox{'}}_{{\textsf{ht}}}{\mathbf{\textsf{b}}}_{{\textsf{hi}}} $$ .The GLMM is expressed as $$ {\textsf{g}}\left({\mu}_{{\textsf{hi}\textsf{t}}}\right)={\mathbf{\textsf{x}}}_{{\textsf{it}}}^{\prime}\beta +\mathbf{\textsf{z}}{\hbox{'}}_{{\textsf{ht}}}{\mathbf{\textsf{b}}}_{{\textsf{hi}}} $$ with link function *g* appropriate to type of outcome (continuous, categorical, count, ordinal) random effects $$ {\mathbf{\textsf{b}}}_{{\textsf{hi}}} $$ to capture serial correlation within participant measures and clustering [138]. The covariates $$ {\mathbf{\textsf{x}}}_{{\textsf{hit}}} $$ are participant characteristics, some of which are time-invariant such as the aforementioned sociodemographic variables; $$ {\mathbf{\textsf{z}}}_{{\textsf{ht}}} $$ are characteristics of park *h* at time *t.* Minimally, the predictor variables are: a single indicator for GROUP, with CNT as referent, three indicators for TIME, corresponding to t = 1, 2, 3 with baseline t = 0 as referent, and GROUP×TIME interactions. A measure of exposure to environmental stimuli is included in participant characteristics. The GLMM allows us to formulate and test hypotheses on functions of the regression parameters β, including: i) point-in-time comparison between INT and CNT, e.g., at each follow-up year; ii) time-averaged comparison between INT and CNT; iii) within group comparison for change over time; and iv) change in INT compared to the corresponding change in CNT via DID. SAS Software v9.4 (Analytics 15.1 or higher) will be used for statistical analyses.

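### The model's time index pools baselines from at least two field seasons and names no calendar-season term, so a year-specific shock biases the DID if entry years differ by arm

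*Protocol article*

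**What the plan says.** The Statistical analysis section sets out one model for all outcomes. "Minimally, the predictor variables are: a single indicator for GROUP, with CNT as referent", followed by "three indicators for TIME, corresponding to t = 1, 2, 3 with baseline t = 0 as referent", and the GROUP×TIME interactions. Park characteristics in the same equation carry the same subscript t. No term for calendar year, field season or entry cohort is named. The baseline equivalence list in that section covers demographic, attitudinal and health variables but not year of entry.

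The dates elsewhere do not share one origin:

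- **Participants:** "We conducted a pilot study in two neighborhoods in 2018" (n = 67). The study then "received funding at the end of the summer in 2019, yielding a truncated field season" (n = 145), and "The first full field season for this study will be 2020".
- **Sample size:** 620 people are to be recruited at t = 0.
- **Control description:** "In June 2018, we conducted extensive inventories of all nine parks at baseline".
- **Measurement protocol, Table 1:** individual and area "measurements that will be obtained annually 2019–2024".
- **Anthropometric and cardio-metabolic measures:** the last year of data collection is given as 2022.

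**The concern.** A DID removes whatever is common to both arms in a given calendar year, provided both arms are compared over the same years. If t = 0 is 2019 for some people and 2020 for others, the comparison is over the same years only when each arm has the same mix of entry years. Otherwise part of any year-specific change in activity or stress (weather, local events, field or device changes) passes into GROUP×TIME and looks like an effect of restoration. This touches the primary physical activity outcome and every hypothesis that compares intervention (INT) with control (CNT) neighborhoods.

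The same undefined index matters for Hypotheses 3 and 6, where park exposures are the predictors. If t is not mapped to a season, the text does not settle which season's park measures belong to which visit.

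**Working it through.** **Step 1. The plan's own baseline figure.** The Sample size section gives attrition of 15%, 10% and 5%: 620 × 0.85 × 0.90 × 0.95 = 450.6, which matches the target of 450. So 620 is the intended number at t = 0.

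**Step 2. Can t = 0 be one season?** People known to have entered before 2020:

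- 145 in 2019, leaving 620 - 145 = 475 (77%) for 2020 or later.
- If the 67 pilot participants of 2018 also count (not stated), 620 - 145 - 67 = 408 (66%) remain for 2020 or later.

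Either way, baseline entry spans at least two seasons.

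**Step 3. Bias formula.** Let c(y) be an additive effect of year y, the same in both arms. Let pI and pC be the shares of INT and CNT entering in 2019, with the rest entering in 2020. There is no true intervention effect.

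- *Personal clock* (t counts years since a person's own entry). The t = 3 bias is (pI - pC) × {[c(2022) - c(2019)] - [c(2023) - c(2020)]}.
- *Study-wide wave* (the baseline wave covers 2019 and 2020, and everyone then shares later waves). The t = 3 year is common and cancels, leaving (pI - pC) × [c(2020) - c(2019)].

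For a shock S in 2020 only, both reduce to **(pI - pC) × S**. The result therefore does not depend on which meaning of t was intended. Under the personal clock, a shock in 2021 contributes nothing at t = 3, because no one with these entry years has a t = 0 or t = 3 visit in 2021.

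**Step 4. Numbers.** Assumptions, none of them in the article: the 620 split 4:5 by parks (276 INT, 344 CNT), 145 entering in 2019, 475 in 2020, and S = 0.35 SD.

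| 2019 entrants, INT / CNT | pI | pC | pI - pC | Bias at t = 3 (SD) | Share of EF 0.35 |
|---|---|---|---|---|---|
| 65 / 80 (balanced) | 0.236 | 0.233 | 0.003 | 0.00 | 0% |
| 87 / 58 (60% INT) | 0.315 | 0.169 | 0.147 | +0.05 | 15% |
| 145 / 0 | 0.525 | 0 | 0.525 | +0.18 | 53% |
| 0 / 145 | 0 | 0.422 | -0.422 | -0.15 | -42% |

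The bias scales with S. In the 60% row, S = 0.2 gives 0.03 SD and S = 0.5 gives 0.07 SD.

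**Step 5. Does a season term cure it?** I fitted the article's fixed effects to noise-free data built as above. They returned the biases in the table. Adding season indicators returned a t = 3 DID of 0 in every row, under both readings of t. GROUP×TIME remained estimable, also with an entry-cohort term added.

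**Step 6. End date.** If 2022 is the last year, a 2020 entrant followed annually has reached only t = 2 (2020 + 2). Their t = 3 needs 2023, which fits Table 1 but not the cardio-metabolic section.

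**The case against.** Several objections have force.

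- **The predictor list is only a minimum.** It is introduced that way, and the article promises to adjust for factors unbalanced between groups and to compile daily weather. A season term is not excluded, but nothing points to one. Entry year is not on the balance list, so an imbalance could go unnoticed. Weather covariates cover heat and rain, not other year-specific changes.
- **The article may intend t as a study-wide wave.** The fallback design, with fresh samples at each time point, reads that way. This stands as an ambiguity, but a baseline wave covering 2019 and 2020 gives the same formula (step 3).
- **Balanced entry removes the bias.** This stands in full. Recruitment in every neighborhood also makes the extreme rows unlikely.
- **Season coding is detail for an analysis plan.** That would hold if the article had left time coding open. It writes out the model and its time indicators.

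A reader might also infer that park data will be attached to the wrong year because the inventory called baseline dates from June 2018. The article does not support that. It never makes that inventory the park value at t = 0 in the model, area measures are repeated annually from 2019, and the inventory covered birds, plants, maintenance and usage, not soundscapes or 360° images. Nor does it establish entry as late as 2021. That comes only from subtracting three follow-up years from Table 1's 2024 end date, while recruitment at later time points is described only as a fallback for high attrition.

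**Conclusion.** The concern holds in a limited form. Baseline entry spans at least two field seasons, the model names no term for season, and the link between t and park season is undefined. It would be too strong to say that calendar shocks necessarily remain in the DID: they do so only if the arms differ in entry-year mix, and the documents do not report that mix. A moderate assumed imbalance with a shock as large as the design effect costs about 0.05 SD, and the extremes are +0.18 and -0.15 SD. These sizes rest on the assumed split by arm, the assumed shock, two entry years only, and year effects that are additive and common to both arms. The change is worth making because it is nearly free and protects the primary contrast.

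**What to change.** In the Statistical analysis section:

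1. Define t, and add field-season (calendar-year) fixed effects beside GROUP, TIME and GROUP×TIME.
2. State that each visit is linked to the park measures of the same season, and which park season serves as baseline for each entry year.
3. Add year of entry to the baseline equivalence list, and report it by arm.
4. Reconcile 2022 as the final collection year with 2019–2024 in Table 1.

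The cost is wording, a merge key and a few individual-level degrees of freedom, with no new data and no change to the sample size. One limitation should be stated. Season equals entry year plus t under a personal clock, so the TIME main effect separates from season only if entry cohorts do not otherwise differ. Under a study-wide wave, later seasons coincide with TIME and only the season contrast within baseline is estimable. GROUP×TIME, which the hypotheses need, stays identified in both cases.

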**Methods:**

The Study of Active Neighborhoods in Detroit is a quasi-experimental, longitudinal panel natural experiment with two conditions (restored park intervention (INT) and control (CNT)) and annual measurements at baseline and 3-years post-restoration. Individuals (sampled within 500 m of an INT/CNT park) serve as the unit of analysis. Restoration (*n* = 4 parks) involves replacing non-native plants and turf with native plants; creating trails; posting signage; and leading community stewardship events. The CNT condition (*n* = 5) is an unmaintained park, matched to INT based on specified neighborhood conditions. Recruitment involves several avenues, with a retention goal of 450 participants. Park measures include plant/avian diversity; usage of the park (SOPARC); signs of care; auditory environment recordings; and visual greenness using 360 imagery. Health outcomes include device-based physical activity behavior (primary outcome); salivary cortisol (secondary outcome); and several downstream health outcomes. Exposure to the INT will be assessed through visual contact time and time spent in the park using GPS data. Changes in health outcomes between years and INT versus CNT will be tested using generalized linear (mixed) models.

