### Survey

Basic demographic data information (age, sex, ethnicity, employment, household composition, length of residence) will be collected at recruitment or when re-contacted at each timepoint. Then, each participant will complete a self-administered paper survey in the privacy of their own home to assess: income, perceptions of the neighborhood [98–102], disease and prescription medication history [103–106], diet [107, 108], perceived stress [74], anxiety and depression symptoms [72, 73] (discussed previously), nature-relatedness [109]; all which were considered potential correlates of device-based PA and stress. Questions about the perceptions of the social and environmental features of neighborhoods have been shown to have moderate to high agreement (rho range = 0.42–0.91) [99]. Family Life, Activity, Sun, Health, and Eating (FLASHE) questions related to diet were reviewed by the scientific experts for consistency with existing, validated measures [108]. The nature-relatedness scale (NR-6) has been shown to demonstrate good internal consistency, temporal stability, and predict happiness, environmental concern, and nature contact [109]. Measures that may serve as confounders include: 1) symptoms of acute illness or infection or prescription medication which could influence biomarker measures; 2) attitudes toward nature using the NR-6, because these may influence behaviors; and 3) perceived safety which may influence stress [110], PA [111, 112], and park usage [113].

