### Park observations and imagery

The positive visual exposures of interest include the presence of people using the park, signage, mowing and other signs of care [114], diversity of plants and birds and greenness. Negative visual exposures include the presence of litter, arson, graffiti and broken windows of buildings along the park perimeter (called signs of disorder). We will employ two methods to obtain these data. First, Audubon volunteers will inventory plants in quadrants and count bird species using point counts less than three hours after sunrise, measuring species abundances [115, 116]. Volunteers will be trained by Audubon, and inter-observer reliability assessed by having two or more observers collect data simultaneously but independently [117]. Plant/bird species richness and biodiversity measurement will employ the well-established Shannon Diversity and Simpson Indexes [118, 119] and Evar Evenness Index [116]. Trained graduate students will also make observations of signs of care and the System for Observing Play and Recreation in Communities (SOPARC) [120]. SOPARC provides an assessment of park users’ PA levels, gender, activity types, and estimated age and ethnicity groupings as well as information on a park’s level of accessibility, usability, supervision, and organization with a high internal correlation between items (r = 0.75) [120], and exhibiting high inter-rater reliability (0.80–0.99) [117]. All nine parks, each of which consists of only one target area due their small size, will be observed twice over one day (9 am-2 pm) during randomly scheduled days without rain in summer months, by two raters. INT and CNT parks will be observed at the same time on different days for parallel observations. Signs of care involve observations (presence/absence) of manmade and natural items in a park and provides a categorical quality rating for each item, which is based on qualitative work in Detroit [114]. Second, we will measure visual greenness and negative visual exposures (signs of disorder) via 360^°^ images captured along each park perimeter, using a mounted camera (Samsung Gear 360). Images will be used to measure visual greenness, by quantifying pixels of greenery using methods we developed [121]. Images will also be used to assess negative exposures using Marco et al.’s neighbor disorder coding protocol [122], which has shown acceptable ICCs (0.41–0.60) for the mean level of subscales of physical disorder and decay and has also been validated (showing high correlations) with physical audits, police impressions, and neighborhood socioeconomic status. This virtual auditing approach has been validated across several samples [123, 124].

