To address missingness in our response data, we will employ strategies for imputation [139]. The techniques described above allow missing at random (MAR). Inverse probability weighting [140] will be investigated to accommodate missing data patterns that are not MAR. To minimize bias in analysis, we will adjust for factors that may be unbalanced between groups and examine the robustness of our conclusions under deviations of model assumptions. Below, we outline specific analyses for each hypothesis to be tested.

#### Hypothesis 1

We will separately evaluate average activity counts/minute and average moderate-to-vigorous minutes over the one-week observation period for each of the data collection periods. The predictor of interest is binary: INT versus CNT.

#### Hypothesis 2

The primary outcome, ‘green PA’, will be average activity counts/minute and average moderate-to-vigorous minutes over the one-week observation period while in parks and greenspaces in Detroit, as a subset of all activity.

#### Hypothesis 3

We hypothesize there will be an association between PA and the visual and auditory exposures. Instead of a binary predictor of interest, we will use continuous predictors for visual and auditory park exposures. Interaction terms between positive and negative exposures will also be assessed, as evidence suggests that negative sounds deplete the restorative benefits of natural sounds, [141] and that parks are often dominated by noise [45, 142].

#### Hypothesis 4

Each stress outcome will be evaluated separately and treated continuously. We will also explore potential mediators (e.g., PA) by adding each to mixed models as fixed terms, and adjusted mediation and partial correlation coefficients explored. We will adjust for prescription medication history and symptoms of acute illness as potential confounders.

#### Hypothesis 5

We will assess relationships with each stress indicator, in turn.

#### Hypothesis 6

We hypothesize there will be an association between each stress indicator and these exposures.

#### Hypothesis 7

We will compare INT and CNT groups from baseline through three-years post-restoration for changes in CRP and A1C (continuously measured) between INT and CNT groups. We will also consider the inclusion of prescription medication history and symptoms of acute illness as potential confounders.

#### Hypothesis 8

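### The general mixed model includes a measure of exposure to environmental stimuli and is not limited to Hypotheses 3 and 6, so the INT-versus-CNT contrast may not estimate the total effect of restoration

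*Protocol article*

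**What the plan says.** All references are to the protocol article. Statistical analysis describes a single generalized linear mixed model for outcomes of every type. Its required terms begin: "Minimally, the predictor variables are: a single indicator for GROUP, with CNT as referent"; indicators for TIME and the GROUP×TIME interactions follow. The next sentence reads: "A measure of exposure to environmental stimuli is included in participant characteristics". The sentence after that lists what will be tested from the model, including "change in INT compared to the corresponding change in CNT via DID".

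The same section then goes through the hypotheses. For Hypothesis 1: "The predictor of interest is binary: INT versus CNT". For Hypothesis 3: "Instead of a binary predictor of interest, we will use continuous predictors for visual and auditory park exposures". Under Hypothesis 4, possible mediators such as physical activity are added to the mixed models as an exploration.

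The exposure measures are described elsewhere. The abstract says: "Exposure to the INT will be assessed through visual contact time and time spent in the park using GPS data". Park observations and imagery says: "The positive visual exposures of interest include the presence of people using the park, signage, mowing and other signs of care", and goes on to plant and bird diversity and greenness. Neighborhood soundscapes adds birdsong and noise levels, extracted for each participant at every time point.

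**The concern.** Hypotheses 1, 2, 4, 7 and 8 ask whether people in restored-park neighborhoods end up with better outcomes than people in control neighborhoods. That is a question about the total effect of restoration. Restoration consists of native planting, trails, signage and events, and it is meant to act through what residents see, hear and do in the park. Exposure measured after restoration is therefore largely part of the effect. A model that holds it fixed compares INT and CNT residents with equal exposure, and the GROUP×TIME coefficient becomes a direct effect that leaves out the exposure pathway.

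The primary outcome is among those affected. A null coefficient from such a model could be reported as restoration having no effect on physical activity when the effect had been moved to the exposure term. In a non-randomized comparison, conditioning on a post-intervention variable can also open a path through unmeasured causes shared by exposure and outcome, and that bias can go either way.

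Hypothesis 2 is the sharpest case. Its outcome is activity in parks and greenspaces, and Table 1 derives both that outcome and time in the park from the same GPS data. Adjusting for time in the park would condition on a near-component of the outcome.

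**Working it through.** **1. Is the exposure measure changed by restoration?** Setting Intervention description beside the exposure sections:

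| Restoration changes | Exposure measure that records it |
|---|---|
| Native planting, turf and cement removed | Greenness, plant diversity |
| Signage, upkeep by residents | Signage and signs of care |
| Bird habitat | Bird diversity, birdsong |
| Trails, guided walks, events | Time in park; possibly time in view of it |

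Table 1 has these tools used annually, so post-restoration values will exist. The model text does not name which measure is used. Some negative stimuli, such as traffic noise across the 500 m grid, may lie off the restoration pathway.

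**2. Does the text restrict the exposure term?** The sentence that includes it carries no condition. The Hypothesis 3 text removes the binary predictor from the exposure analysis; it does not remove exposure from the group analyses. No other section does so.

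**3. Reproducing the planned power.** Inputs from Sample size: effect 0.35 SD, two-sided 5%, 50 participants per park, 4 INT and 5 CNT parks (200 and 250 people), r = 0.35, ρ = 0.004. Two standard forms of the variance of the difference-in-differences, in SD units:

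- A, design effect on change scores: SE = √{2(1 − 0.35) × [1 + 49 × 0.004] × (1/200 + 1/250)} = √(1.3 × 1.196 × 0.009) = 0.1183. Then z = 0.35/0.1183 = 2.96 and power = Φ(2.96 − 1.96) = 84%.
- B, park-level variance not cancelled by differencing: SE = √{2[(0.996 × 0.65)/50 + 0.004] × (1/4 + 1/5)} = 0.1235. Then z = 2.83 and power = 81%.

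The stated 82% lies between them. The attrition figures agree too: 620 × 0.85 × 0.90 × 0.95 = 450.6. The plan's power therefore refers to the total effect of 0.35 SD.

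**4. What remains after conditioning on exposure.** Let p be the share of the effect that passes through the chosen measure. The documents give no value, so p is an assumption and a range is shown. The coefficient is 0.35 × (1 − p). With the standard errors held unchanged:

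| p | Coefficient (SD) | Power, A | Power, B |
|---|---|---|---|
| 0% | 0.35 | 84% | 81% |
| 25% | 0.26 | 60% | 57% |
| 50% | 0.175 | 32% | 29% |
| 75% | 0.09 | 12% | 11% |
| 100% | 0 | 5% | 5% |

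**5. Simulation.** With 2,000 simulated trials for each share from 25% to 100%, and restoration assumed to shift exposure by 1 SD, the estimate without the exposure term averaged 0.35 throughout, with rejection rates of 0.85 to 0.88. With the term, it averaged 0.26, 0.17, 0.08 and 0.00, with rejection rates of 0.59, 0.32, 0.12 and 0.07. The fits were ordinary least squares that ignored the small park-level variance. The simulation confirms the algebra under assumed mediation; it is no evidence on how large the mediated share is.

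**The case against.** The strongest reply is that the model paragraph is a template. It has to serve all eight hypotheses, and Hypotheses 3 and 6 need exposure terms. Exposure is not among the terms listed as the minimum. The hypothesis-by-hypothesis text names a binary predictor for Hypothesis 1, substitutes continuous exposures for it in Hypothesis 3, and lists exposure under none of the INT-versus-CNT hypotheses. Mediators appear as a separate exploratory step under Hypothesis 4. Read literally, the general sentence would also put GROUP and exposure together in Hypothesis 3, which fits poorly with replacing one by the other. Finally, this is a condensed article, and covariate sets are often settled in an analysis plan that is not shown.

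Much of this stands. The template reading is plausible and probably reflects the intent. It does not dispose of the point, because the issue is an unrestricted statement in the text, not a missing detail. An analyst following the paragraph as written would fit exposure and the difference-in-differences together.

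Two stronger readings are tempting and not supported. The first is that the plan also adjusts for post-restoration perceived safety and nature attitudes. The Survey section says only that measures such as "perceived safety which may influence stress" may serve as confounders. Statistical analysis compares both variables between groups at baseline and controls for substantive differences found there. No section says that later values enter the group models. The second is that the plan certainly adjusts the effect away. The exposure measure is unnamed, the mediated share is unknown, bias can act in either direction, and the standard error would itself change when a covariate correlated with GROUP is added.

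**Conclusion.** The point holds as a conditional one. The text places an exposure measure in the model from which the INT-versus-CNT contrast is tested and does not limit it to Hypotheses 3 and 6. So far as the chosen measure is taken after restoration and altered by it, the GROUP×TIME coefficient in Hypotheses 1, 2, 4, 7 and 8 is not the effect that the Objectives state and the Sample size section powers.

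The loss equals the mediated share. The power figures in the table are illustrations that rest on assumed shares, an unchanged standard error, and mediated and total effects of the same sign. Complete loss occurs only under full mediation. It deserves correction before analysis because it reaches the primary outcome and could produce a misleading null result.

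**What to change.** Add to the model paragraph of Statistical analysis: post-restoration exposure measures enter only the models for Hypotheses 3 and 6 and separately labelled exploratory mediation analyses; the INT-versus-CNT models for Hypotheses 1, 2, 4, 7 and 8 contain GROUP, TIME, GROUP×TIME and covariates that restoration cannot change. Where perceived safety or NR-6 is adjusted for because of imbalance at baseline, specify its t = 0 value.

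The cost is a sentence or two of text. No new data, measurements or participants are needed, and the exposure analyses are kept.
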